#### **4.10 Duration of Therapy**

The end of protocol therapy will occur if:

- Inter-current illness that prevents further administration of treatment
- Unacceptable adverse event(s)
- Subject decides to withdraw from the study, or
- General or specific changes in the patient's condition render the subject ineligible for further treatment at the discretion of the investigator or treating physician

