#### **4.13 Subject Replacement**

Three subjects within dose levels -1 and 0 must be observed for 90 days before accrual to the next higher dose level may begin. For level 1, 7 patients must be observed for 90 days before accrual to the next higher dose level. If a subject is withdrawn from the study prior to completing therapy without experiencing a dose limiting toxicity prior to withdrawal, an additional subject may be added to that dose level. Subjects missing 3 or more radiation treatments due to toxicity will not be replaced since these subjects will be considered to have experienced a dose limiting toxicity.

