## 5.5 Removal of Subjects from Study

Subjects can be taken off the study treatment and/or study at any time at their own request, or they may be withdrawn at the discretion of the investigator for safety, behavioral or administrative reasons. The reason(s) for discontinuation will be documented and may include:

- 
- 5.5.1 Subject voluntarily withdraws from treatment (follow-up permitted);
  - 5.5.2 Subject withdraws consent (termination of treatment and follow-up);
  - 5.5.3 Subject is unable to comply with protocol requirements;
  - 5.5.4 Subject demonstrates disease progression (unless continued treatment with study drug is deemed appropriate at the discretion of the investigator);
  - 5.5.5 Subject experiences toxicity that makes continuation in the protocol unsafe
  - 5.5.6 Treating physician judges continuation on the study would not be in the subject's best interest;
  - 5.5.7 Subject becomes pregnant (pregnancy to be reported along same timelines as a serious adverse event);
  - 5.5.8 Development of second malignancy (except for basal cell carcinoma or squamous cell carcinoma of the skin) that requires treatment, which would interfere with this study
  - 5.5.9 If a research subject cannot be located to document survival after a period of 2 years, the subject may be considered "lost to follow-up." All attempts to contact the subject during the two years must be documented and approved by the Data Monitoring Committee.

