## 10.2 Phase 1 waiting periods

Fraction reduction for this phase 1 clinical trial will not occur until sufficient waiting has occurred after a cohort has been treated. A period of 90 days must pass before further fraction reduction for the purpose of assessing toxicity. If 90 days have passed without a DLT at a dose level, the trial will be allowed to the next level, so long as either criteria for defining the MTD or criteria for further fraction reduction is not reached. If the maximum number of patients are enrolled to a given fraction level, yet criteria for follow-up is not reached in a representative sample of patients, further enrollment to the protocol will be suspended until adequate follow-up is reached. No action will be taken for Grade 1 or Grade 2 toxicities. If any 2 Grade 3 toxicities occur within a dose level likely or definitely related to radiation therapy, the trial will be terminated with reporting of DLT at that dose level. Any Grade 4 or Grade 5 toxicity found to be likely or definitely related to treatment will result in termination of the trial with reporting of DLT at that dose level.

Grade 3 toxicities likely or definitely related to protocol therapy will result in action in schema provided below:

[figure not shown]

For level -1, if a Grade 3 toxicity occurs, the trial will be terminated with reporting of DLT.

For level 0, if a Grade 3 toxicity occurs, a step de-escalation will occur to level -1. If no grade 3 toxicities are experienced at level 0, the trial will proceed to level 1.

---

For level 1, if there are no Grade 3 toxicities after initial enrollment of 7 patients, an additional 8 patients will be enrolled. If there is no grade 3 toxicity after enrollment of an additional 8 patients, the trial will proceed to level 2. If there is a 1 grade 3 toxicity in the additional 8 patients, the trial will proceed to level 2 at the discretion of the PI and DSMC.

For level 1, if there is 1 Grade 3 in the initial 7 patient cohort, an additional 8 patients will be enrolled. If there is an additional Grade 3 toxicity at this level, the trial will be terminated with reporting of DLT. If there are no further grade 3 toxicities in the additional 8 patients, proceeding to the next level will be done at discretion of the DSMC and PI.

For level 1, if there are 2 grade 3 toxicities in the initial 7 patient cohort, the trial will be terminated with reporting of DLT.

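### Patients lost before day 90 (level 1's additional 8, all of level 2), or stopped early for non-toxicity reasons but still on study, count as event-free and favour fewer fractions

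*Protocol*

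**What the plan says.** **Replacement (4.13).** The only trigger is "If a subject is withdrawn from the study prior to completing therapy without experiencing a dose limiting toxicity prior to withdrawal". In that case "an additional subject may be added to that dose level", so replacement is permitted but not required. Missing three or more treatments because of toxicity is treated as a dose-limiting toxicity, and such a patient is not replaced.

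**Observation (4.13).** "Three subjects within dose levels -1 and 0 must be observed for 90 days before accrual to the next higher dose level may begin". The corresponding number at level 1 is 7; none is given for level 2.

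**Decision counts (10.2).** At level 1, "if there are no Grade 3 toxicities after initial enrollment of 7 patients, an additional 8 patients will be enrolled". With no grade 3 toxicity after those 8 are enrolled, the trial moves to level 2. With one in the 15, moving on is at the discretion of the PI and DSMC. Two grade 3 toxicities at a level end the trial. Level 2 also enrols 7 and then 8. Section 10.2 adds a 90-day wait. It also suspends enrolment if a level is full but follow-up is not yet adequate in a representative sample, with no number attached.

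**Ways of stopping treatment without leaving the study.** Section 4.10 lists "Inter-current illness that prevents further administration of treatment" as a reason for therapy to end. Section 5.5.1 lets a patient give up treatment and remain in follow-up.

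**The concern.** A level is to be judged on patients who received its course and were watched for 90 days afterwards. Two kinds of patient cannot supply that evidence and fall outside the replacement rule:

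- those who finish therapy and are then lost, withdraw or die of another cause before day 90;
- those who stop radiation early for a non-toxicity reason but stay on study, possibly after very few fractions.

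Because 10.2 asks only whether grade 3 events have occurred among a stated number of enrolled patients, a patient with no recorded event meets the condition whether or not an event could have been seen. This dilutes the observed toxicity frequency. At level 1 it eases the step to 5 fractions. At level 2 it eases the conclusion that 5 fractions is tolerated, which is one of the two completion criteria of the primary endpoint (10.1).

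**Working it through.** **The plan's own figures.** The cohort sizes in the schema's step table give a minimum of 3 + 7 + 7 = 17 and a maximum of 3 + 15 + 15 + 15 = 48, as stated. The protocol gives no target toxicity rate or error rate, so there is no operating characteristic to reproduce.

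**Who is protected and who is not.**

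| Group | 90-day count in 4.13 | Early loss kept out? | Treatment amount required? |
|---|---|---|---|
| Levels -1 and 0, required 3 | yes | yes | no |
| Level 1, required 7 | yes | yes | no |
| Level 1, additional 8 | none | no | no |
| Level 2, all 15 | none | no | no |

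**Effect on a 15-patient level.** Let p be the true grade 3 rate (assumed) and k the number of the 15 who are uninformative but counted (assumed). If those k have no chance of showing an event, then

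P(at most 1 event) = (1-p)^(15-k) + (15-k) × p × (1-p)^(14-k).

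For p = 0.20:

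- k = 0: 0.8^15 + 15 × 0.2 × 0.8^14 = 0.0352 + 0.1319 = 0.167
- k = 3: 0.8^12 + 12 × 0.2 × 0.8^11 = 0.0687 + 0.2062 = 0.275

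| k | p = 0.10 | p = 0.20 | p = 0.30 |
|---|---|---|---|
| 0 | 54.9% | 16.7% | 3.5% |
| 1 | 58.5% | 19.8% | 4.7% |
| 2 | 62.1% | 23.4% | 6.4% |
| 3 | 65.9% | 27.5% | 8.5% |
| 8 (extreme: only level 1's required 7 are informative) | 85.0% | 57.7% | 32.9% |

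These are chances of not being stopped by the two-event rule. Moving from level 1 to level 2 without recourse to discretion needs zero events. At p = 0.20 that chance is 0.8^15 = 3.5% for k = 0, and 0.8^14 = 4.4%, 0.8^13 = 5.5% and 0.8^12 = 6.9% for k = 1, 2 and 3.

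**Why these are upper bounds.** A patient lost late in the window has already been at risk for most of it. Suppose, for illustration, that each of 3 such patients keeps half the event probability (0.1 instead of 0.2):

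- P(0) = 0.0687 × 0.9^3 = 0.0501
- P(1) = 0.2062 × 0.729 + 0.0687 × 3 × 0.1 × 0.81 = 0.1503 + 0.0167 = 0.1670
- total = 21.7%, against 27.5% at the bound and 16.7% with full information.

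**Level 0.** Proceeding requires no grade 3 event. With p = 0.20 and 3 informative patients, the chance is 0.8^3 = 51.2%. If one of the 3 was observed for 90 days after so little treatment that an event was not possible, it is 0.8^2 = 64.0%. This comparison applies only to an under-treated patient. With one of 3 lost before day 90, only two have been observed and level 1 cannot open on them.

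**The case against.** The strongest reply is that the protocol nowhere says an unobserved patient counts as toxicity-free. The 10.2 decision figure is not reproduced in the text at hand, and an evaluable set may be defined in a statistical analysis plan. This stands in part: the reading comes from how the rules are worded, not from an explicit statement. But 10.2 does state its conditions as absence of grade 3 events after a number of patients are enrolled. The replacement and advancement rules also govern live accrual, and the protocol has already fixed them.

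Second, safeguards exist: the 90-day count in 4.13, the waiting period and suspension clause in 10.2, and the rule that three or more treatments missed for toxicity is a dose-limiting toxicity. All of these stand and they narrow the point. They do not reach level 1's additional 8 or level 2 with any number, and none of them deals with treatment cut short for a non-toxicity reason. Patients who stop treatment under 5.5.1 do remain observable, but for a course they did not receive.

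Third, the toxicity rates and the numbers lost are assumptions, and not being stopped is not the same as advancing. Both are correct, and the figures should be read that way.

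A reader might also infer more than the documents support:

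- *That early losses distort every level.* The 4.13 observation count excludes them from the required 3 and 7.
- *That one loss at level -1 leaves it impossible to clear.* The schema table shows 3 there, but the Section 4.1 table gives 3 as a minimum.
- *That the error always runs toward fewer fractions.* It does so where such patients are counted. Where the observation count applies, an early loss holds the trial back instead.

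**Conclusion.** The point holds in a limited form. As worded, 4.13 and 10.2 let two kinds of uninformative patient add to the denominator as event-free: those lost before day 90 among level 1's additional 8 or at level 2, and, at any level, those stopped early for non-toxicity reasons while remaining on study. Where they are counted, the decision leans toward fewer fractions. At level 2 no further reduction follows, so only the tolerability conclusion is affected.

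The size is moderate and conditional. At an assumed grade 3 rate of 20% with 1 to 3 such patients of 15, the chance of escaping the stopping rule rises by at most about 3 to 11 percentage points (16.7% to between 19.8% and 27.5%). At 30% the rise is from 3.5% to at most 8.5%. The calculation concerns grade 3 events only and gives the affected patients no chance of an event. The point should be settled, since the correction is a matter of wording.

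**What to change.** In 4.13, define a toxicity-evaluable patient as either:

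- one with a toxicity counted by 10.2 at any time after the first fraction; or
- one who received the level's planned course, or missed treatments because of toxicity, and was observed through day 90.

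Require replacement of patients who are non-evaluable for non-toxicity reasons, whether lost before or after the end of therapy. Do not replace patients whose treatment was cut short by toxicity: they are informative, and replacing them would bring in a bias of its own. The existing rule on three or more treatments missed for toxicity can stay as it is.

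In 10.2, apply the counts to evaluable patients, including level 1's additional 8 and all of level 2. This gives the follow-up condition a number in place of the unquantified representative sample.

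The cost is wording in two sections, a few replacement patients and some waiting time. Levels 1 and 2 already use all 15 places (7 + 8), so the protocol should say that replacements may exceed the 15-per-level and 48-patient maxima.

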#### **4.14 R.T. Quality Assurance Reviews**

[name], along with a medical physicist, will perform an RT Quality Assurance Review after complete data for the first 15 cases enrolled has been obtained. They will perform the next review after complete data for the next 15 cases enrolled has been obtained. The final cases will be reviewed within 3 months after this study has reached the target accrual or as soon as complete data for all cases enrolled has been received, whichever occurs first.

### **5.0 STUDY PROCEDURES**

#### **5.1 Screening/Baseline Procedures**

Assessments performed exclusively to determine eligibility for this study will be done only after obtaining informed consent. Assessments performed for clinical indications (not exclusively to determine study eligibility) may be used for baseline values even if the studies were done before informed consent was obtained.

All screening procedures must be performed within 30 days prior to registration unless otherwise stated. The screening procedures include:

##### **5.1.1 Informed Consent**

##### **5.1.2 Medical history**

Complete medical and surgical history, history of infections

##### **5.1.3 Demographics**

Age, gender, race, ethnicity

##### **5.1.4 Review subject eligibility criteria**

##### **5.1.5 Review previous and concomitant medications**

##### **5.1.6 Physical exam including vital signs, height and weight**

Vital signs (temperature, pulse, respirations, blood pressure), height, weight

##### **5.1.7 Performance status**

Performance status evaluated prior to study entry according to the ECOG

##### **5.1.8 Adverse event assessment**

All acute and late adverse events from protocol radiation therapy will be reported and scored for severity using the NCI Common Terminology Criteria for Adverse Events (CTCAE) version 4.0. A copy of the CTCAE v4.0 can be downloaded from the CTEP home page (<http://ctep.info.nih.gov>).

#### **5.1.1 Laboratory work - Pregnancy test (for females of child bearing potential)**

All females of childbearing potential will undergo either a urine qualitative  $\beta$ -HCG level or serum quantitative  $\beta$ -HCG level to show that they are not currently pregnant.

---

**5.1.2 Tumor assessment**

Tumor assessment will be performed by physical examination, CT-scan of the neck, and flexible laryngoscopy.

**5.1.3 QoL Questionnaires and Symptom Questionnaires**

EORTC QLQ-C30, H&N 35, MDADI, VHI, EQ-5D, and cost and convenience questionnaire. These forms will be referred to collectively as QoL Questionnaires described in section 6.

**5.2 Procedures during Treatment****5.2.1 Prior to Each Treatment Cycle**

- Clinical Assessment, vital signs

**5.2.2 Day 1**

- Initiation of CyberKnife radiotherapy
- Clinical Assessment

**5.2.3 Weekly during treatment (as applicable for fractionation)**

- Clinical Assessment
- Toxicity Assessment

**5.2.4 Four weeks after treatment termination**

- Interim history
- Physical exam, vital signs
- Flexible laryngoscopy to assess tumor response and toxicity
- Quality of life and voice quality assessment

**5.3 Follow-up Procedures**

After initial follow-up at four weeks after completion of radiation therapy, subjects will be followed every 3 months for the first year, every 6 months for the second year, and annually for years 3, 4, and 5. These protocol mandated procedures will occur at each follow-up:

- Interim history
- Physical exam, vital signs
- Laryngoscopy to assess tumor response and toxicity
- Quality of life and voice quality assessment
- CT-scan of neck with tumor measurements

## 5.4 Time and Events Table

|                                                                                                                                     | Pre-study | Day 1 | Weekly | 4 weeks after completion | Follow-up
*B |
|-------------------------------------------------------------------------------------------------------------------------------------|-----------|-------|--------|--------------------------|-----------------|
| Assessment                                                                                                                          |           | X     | X      | X                        |                 |
| Informed Consent                                                                                                                    | X         |       |        |                          |                 |
| History and Physical Exam                                                                                                           | X         |       |        | X                        | X               |
| Performance Status                                                                                                                  | X         | X     |        | X                        | X               |
| Toxicity (include DLT) Evaluations                                                                                                  |           | X     | X      | X                        | X               |
| CT-scan based tumor measurements                                                                                                    | X         |       |        |                          | X               |
| Laryngoscopy                                                                                                                        | X         |       |        | X                        | X               |
| Chest x-ray or Chest CT-scan                                                                                                        | X         |       |        |                          |                 |
| Urine $\beta$ -HCG (females)                                                                                                        | X         |       |        |                          |                 |
| Thyroid stimulating hormone (TSH)                                                                                                   | X         |       |        |                          | X (yearly)      |
| Patient Cost and Convenience Form                                                                                                   | X         |       |        |                          |                 |
| HR-QoL/Utility Forms *A
1) EQ-5D
2) EORTC-QLQ C30 + HN 35
3) VHI
4) MDADI
5) Cost and convenience questionnaire (*A) | X         |       |        |                          | X               |
|                                                                                                                                     |           |       |        | X                        | X               |
|                                                                                                                                     | X         |       |        | X                        | X               |

\* A. Cost and Convenience Questionnaire will only be administered at the first available follow up. All other QoL surveys will take place as stated per this row.

\*B. After initial follow-up at 4 weeks after completion of radiation therapy, subjects will be followed every 3 months for the first year, every 6 months for the second year, and annually for years 3, 4, and 5. These protocol mandated procedures will occur at each follow-up:

- Interim history
- Physical exam, vital signs
- Laryngoscopy to assess tumor response and toxicity
- Quality of life and voice quality assessment
- CT-scan of neck with tumor measurements

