## 8.2 Cost effectiveness data collection:

Health care utilization data needed to assess costs will be obtained from treatment records. Additionally, in order to assess the treatment related indirect costs and patient out of pocket costs, a form will be administered during the last week of treatment or at the first available follow up visit after completion of radiation treatment (see Appendix VII).

- Hospitalizations: For hospitalizations with physician billing records, inpatient physician costs will be estimated by applying Medicare payment rates under the RBRVS-based Medicare Fee Schedule to billed procedures in the physician billing records.
- Treatment Cost: Direct costs of radiation treatment including consultation, simulation, treatment planning, and treatment delivery. Patient bills related to treatment will be obtained and estimated by total billed charges adjusted by facility-specific cost-to-charge ratio from Medicare cost reports as described above.
- Emergency Room visits: The date of ER visit and name of the facility, and whether the ER visit resulted in a hospital admission. ER costs will be estimated using Medicare average payment rates for facility and physician charges, using the merged MEDPAR and MBS data as described above.
- Physician and Clinic Visits: The date of the visit, the name of the physician or physician clinic, and the service provided (physician exam, lab test, physical therapy, etc.). Costs for physician and clinic visits will be calculated based on billing records obtained for such visits, using Medicare payment rates for procedures indicated in the clinic billing records.
- Medications: Prescription drugs used, including dosage strength and frequency of administration. Information about name, dose, and frequency of all prescription medications will be recorded. The medications used by the study patients will be assigned an NDC drug code. Unit costs for these drugs will be estimated as the “AWP” price published in the Red Book less 15%. Outpatient drug costs will be calculated by multiplying unit cost by the number of pills used per day times the length of time the patient received the medication. Note that costs of drugs administered through a clinic (e.g., reimbursed under Medicare Part B) are included under “clinic visit costs” and inpatient drug costs are included under “inpatient facility costs.”

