With the improved utilization of endoscopic laser surgery, a similar study assess the quality of life of patients undergoing laser surgery versus radiotherapy. Their health-related quality of life was assessed via EORTC-QLQ C30 and H&N 35 forms. The results of this study showed that both modalities achieved excellent quality of life in the treatment of early laryngeal tumors.

While numerous other studies use a wide range of questionnaires to assess health-related quality of life, we chose to use the EORTC-QLQ C30 and H&N 35 similar to the above-mentioned trials to aid in future comparisons.

All HR-QoL will be used for descriptive purposes only due the single arm phase I nature of this protocol.

Additionally, in order to calculate the indirect costs associated with hypofractionated radiation treatment, a single administration of a short economic questionnaire will take place at the end of radiation treatment or first available follow up or whichever occurs first. This questionnaire which has been adapted for administration in the United States has been used in economic assessments in rural Canadian cancer health service research.

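### The single cost and convenience questionnaire is scheduled before treatment in two places and at or after the end of treatment in three, and a pre-treatment form cannot record treatment costs

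*Protocol*

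**What the plan says.** Five statements in the protocol fix when this form is given.

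- **Section 5.1.3 (QoL Questionnaires and Symptom Questionnaires)**, within the screening and baseline procedures, lists "EORTC QLQ-C30, H&N 35, MDADI, VHI, EQ-5D, and cost and convenience questionnaire". The opening of Section 5.1 sets the window for that list: "All screening procedures must be performed within 30 days prior to registration unless otherwise stated".
- **Section 5.4, stand-alone row** "Patient Cost and Convenience Form": the only mark is in the Pre-study column.
- **Section 5.4, HR-QoL/Utility Forms row, item 5**, which carries the *A marker. The footnote reads "Cost and Convenience Questionnaire will only be administered at the first available follow up".
- **Section 8.2**: "a form will be administered during the last week of treatment or at the first available follow up visit after completion of radiation treatment".
- **Section 9.1**: "a single administration of a short economic questionnaire will take place at the end of radiation treatment or first available follow up", with the addition that the earlier of the two applies.

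Section 8.2 gives the form's purpose: "in order to assess the treatment related indirect costs and patient out of pocket costs".

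**The concern.** The first two statements put the form before any radiation has been delivered. The other three put it at or after the end of treatment. Section 9.1 allows one administration, so the two sets cannot both be met.

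The early time also defeats the form's purpose, since costs that have not arisen cannot be reported. Cost-effectiveness is secondary objective 2.2.6. Hospital, treatment, emergency, clinic and drug costs in Section 8.2 come from records and bills. This form is the only source the protocol names for indirect and out-of-pocket costs. The protocol also gives convenience and cost savings as reasons for hypofractionation (Sections 1.1 and 1.3), so the costs that patients bear themselves are of direct interest.

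**Working it through.** There is no figure to reproduce. The check is a side-by-side reading of each place that schedules the form.

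| Place | Time given | Relative to treatment |
|---|---|---|
| 5.1.3, with the 5.1 window | Within 30 days before registration | Before |
| 5.4, stand-alone row | Pre-study mark only | Before |
| 5.4, HR-QoL row item 5 with footnote *A | First follow-up visit only | After |
| 8.2 | Final treatment week, or first follow-up visit | At the end, or after |
| 9.1 | Once, at end of radiation or first follow-up, whichever is earlier | At the end, or after |

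1. **Count.** Two statements are before treatment and three are at or after its end.

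2. **Is it one instrument?** The names vary (form, questionnaire, short economic questionnaire). No section describes a separate baseline version, and Section 9.1 speaks of a "single administration of a short economic questionnaire will take place at the end of radiation treatment or first available follow up". On the text, it is one form given once.

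3. **What a screening form can contain.** Section 3.0 bars study treatment before registration, and screening precedes registration. At screening a patient has therefore had 0 of the 15, 10 or 5 fractions at levels 0, 1 and 2 (0 of 16 at level -1). A form completed then holds no cost of protocol treatment at any level.

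4. **Do the later statements agree?** Not fully. Footnote *A permits only a follow-up visit. The end of radiation always comes before the first follow-up, which Section 4.11 sets at four weeks, so the Section 9.1 rule points to the end of radiation unless that form is missed. Sections 8.2 and 9.1 describe nearly the same window. The remaining difference is between those two sections and the footnote, and it is small beside the pre-treatment conflict.

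5. **Does the finding depend on the table layout?** No. The HR-QoL row is broken in the available text and a mark may have moved. Section 5.1.3 still conflicts in running text with footnote *A, Section 8.2 and Section 9.1.

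**The case against.** The strongest reply is that the protocol largely resolves this itself. Section 5.1 qualifies its screening window by allowing for exceptions, and footnote *A states one, in restrictive terms. Section 5.1.3 defines a collective name for all the questionnaires, which may be why this form appears there. Three specific timing statements outweigh a list entry and one table mark. Direct costs come from records in any case, and the objective concerned is one of several secondary ones in a single-arm phase I study of 17 to 48 patients.

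Much of this stands. It makes the later time the likelier intention and limits what is at stake. It does not remove the conflict. The stand-alone row carries no *A marker, Section 5.1.3 has no cross-reference to the footnote, and the allowance for exceptions does not explain why a form about treatment costs is listed as a screening procedure at all.

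Three stronger readings are tempting, and the protocol does not support them:

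- *A site using the events table would have no later form.* Item 5 of the HR-QoL row, read with footnote *A, does schedule the form at follow-up.
- *The patient-cost data would be lost for everyone.* That requires staff to follow Section 5.1.3 or the stand-alone row throughout and to ignore three explicit statements. Nothing in the protocol makes this likely.
- *Mixed timing would bias the cost estimate downward.* No section plans to pool forms from different times. A form completed at screening would understate treatment cost, but a four-week form could include costs that an end-of-radiation form would not. The overall direction would depend on the mix and on the form's recall wording, which is not available here.

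**Conclusion.** The schedule is wrong as written. The same once-only form is placed both before treatment and at or after its end, and the earlier placement cannot serve the stated purpose.

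The consequence is conditional and applies patient by patient: whoever completes the single form at screening contributes nothing to the indirect and out-of-pocket cost input to objective 2.2.6. The number of such patients cannot be derived from the protocol. The primary endpoint, the safety rules and the record-based direct costs are untouched.

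This rests on two assumptions. The several names are taken to denote one instrument, as Section 9.1 implies. The form's content is taken to match the purpose in Section 8.2, because the form itself is not available here.

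**What to change.** - Delete the questionnaire from the Section 5.1.3 list.
- Remove the Pre-study mark from the stand-alone row in Section 5.4, or delete that row, since item 5 of the HR-QoL row already covers the form.
- Choose one time at or after the end of treatment for all dose levels and word it identically in the table, footnote *A, Section 8.2 and Section 9.1.

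Either later time is acceptable. The end of radiation covers the whole course with shorter recall, but the table has no end-of-radiation column, so one would have to be added or a note placed on the weekly column. The first follow-up visit agrees with footnote *A. If it is chosen, name it as the four-week visit, because the table shows that visit in a column separate from Follow-up.

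The change costs wording and one table row. It adds no visit and removes one form from screening.
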